### Data management

To protect participant’s confidentiality, only pseudonyms are used for all data documentation, sample markings, and communication with third parties (e.g., laboratories, collaboration partners). Clinical data are collected in source documents and electronic case report forms (Research Electronic Data Capture database). Database entries are automatically checked for data format and appropriate range. We do not rely on an additional independent monitoring for this is a single-center, exploratory study. Due to the minimal risks of the probiotic intervention, a data monitoring committee is deemed unnecessary. We will submit modifications to this protocol to the institutional review board, participants, and investigators. After completion of the study, data will be stored for 10 years and then be deleted.

We do not ask participants for broad consent. Thus, we will only use data and samples for the hypotheses stated in this protocol and will not provide them for ancillary studies.

After completion of this study, the results will be expounded to participants, presented on scientific conferences, published in peer-reviewed journals, and circulated to physicians and the medical laity. We will comply with the official eligibility guidelines for authorship for all publications and do not intend to use professional writers.

### Data analysis

A confirmatory analysis will be conducted based on the intention-to-treat (ITT) population, defined by the ITT principle. We want to show that the intervention group is superior to the control, i.e., the mean nocturnal systolic BP at 8 weeks after the start of treatment adjusted for the baseline value is lower in the intervention group than in the control group. An analysis of covariance (ANCOVA) adjusted for baseline systolic BP values using group allocation as a factor will be applied. The global two-sided significance level is 0.1. Missing values will be replaced using multiple imputation [22].

A sensitivity analysis to the primary efficacy ANCOVA model will be applied with additional covariates/factors given by age and sex. Subgroup analysis is planned for sex. Descriptive methods will be used for the analysis of all clinical, demographic, and safety parameters, including the calculation of appropriate summary measures of the empirical distribution as well as 95% confidence intervals and calculation of descriptive two-sided *p* values. A safety analysis of frequencies and rates of adverse events will be performed. Additionally, sensitivity analyses will be conducted for different populations (per-protocol population, patients with complete cases). Interim analyses are not included in our analysis plan. All analyses will be done using validated statistical software.

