### Complete list of inclusion criteria

Men and postmenopausal women (ratio 1:1)50–75 years of ageGrade 1 hypertension, defined as resting office blood pressure of 140–159 and/or 90–99 mmHg according to the European Societies of Cardiology and Hypertension (ESC/ESH) guidelines [20]Hypertension can be treated or untreatedBody mass index between 18.5 and 34.9 kg/m^2^

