### Randomization

Eligible patients are included after the successful screening. Randomization is done by the supplier (see below) based on the lists generated with an ad hoc SAS® program (sex stratification, randomly varying block sizes). Based on these lists, the supplier delivers sequentially numbered boxes containing sachets to the study center without any information on group allocation. Thus, strictly concealed allocation and complete blinding are ensured. A person of trust from the study center not involved in the study has access to sealed envelopes for each participant, thereby enabling disclosure of group allocation if necessary.

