### Power calculation

Based on the above mentioned meta-analysis [9] and on our own unpublished data (NCT02509962, NCT02971787), we estimate a mean decrease in systolic BP of 3.8 mmHg with a standard deviation of 5.0 mmHg in the probiotic group. In addition, we assume that the placebo group will have the same systolic BP baseline value and a small decrease in the mean systolic BP of 0.2 mmHg with the same standard deviation. That leads to a standardized effect size between groups of (3.8 − 0.2)/(√2 × 5.0) ≈ 0.51. The required sample size to find a significant effect with a power of 0.8 at a two-sided significance level of 0.1 is given by 98 patients (49 per treatment arm, calculated with ADDPLAN, version 6.1). To account for approximately 10% dropout, the total number of patients to be recruited is 110 (98/110 ≈ 0.9).

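### Randomisation is stratified by sex but the primary ANCOVA omits sex; if sex predicts week-8 nocturnal systolic BP beyond baseline, the primary test is mildly conservative

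*Protocol article*

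**What the plan says.** In the Randomization section, the allocation lists use "sex stratification, randomly varying block sizes". The inclusion criteria plan for as many men as women.

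The Data analysis section then fixes the primary model: "An analysis of covariance (ANCOVA) adjusted for baseline systolic BP values using group allocation as a factor will be applied". Sex is not in it. Sex appears in the next paragraph, in a secondary role, "A sensitivity analysis to the primary efficacy ANCOVA model will be applied with additional covariates/factors given by age and sex", and once more as "Subgroup analysis is planned for sex". The test is governed by "The global two-sided significance level is 0.1".

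The terms of the primary model are stated, so this is a choice made in the article and not a detail left to an unseen analysis plan. No reason is given for leaving out the only stratification factor.

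**The concern.** Blocked randomisation within sex forces near-equal numbers of men in the two arms, and likewise of women. Any sex difference in outcome therefore largely cancels from the treatment comparison. An ANCOVA without sex does not know this: it treats the sex difference as random error and reports a standard error that includes it. Where sex carries information about the week-8 value beyond the baseline value, the interval is wider and the p value larger, on average, than the design warrants.

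At stake is some precision in the one analysis that the Data analysis section calls confirmatory. Planned power is 0.80, and the Discussion describes recruitment as difficult, so precision cannot easily be bought with more patients. If the models with and without sex fell on opposite sides of 0.10, the current text would let the one that ignores the stratification decide, and changing the primary model after unblinding would not be credible.

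**Working it through.** **Inputs from the protocol article.** Power calculation: "we estimate a mean decrease in systolic BP of 3.8 mmHg with a standard deviation of 5.0 mmHg in the probiotic group"; a 0.2 mmHg fall on placebo with the same SD; effect size (3.8 − 0.2)/(√2 × 5.0); 49 per arm, "with a power of 0.8 at a two-sided significance level of 0.1". The difference is 3.6 mmHg and the SD implied by that denominator is √2 × 5.0 = 7.07 mmHg. Whether the √2 belongs there is a separate question; 7.07 is used because it is the SD behind the planned sample size.

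**Input not in the documents.** Let *g* be the sex difference in week-8 nocturnal systolic BP after adjustment for baseline. No figure is given, so *g* is assumed to be 0, 2 or 4 mmHg.

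**Step 1: reproduce the plan's figure.** d = 3.6/7.07 = 0.509. At two-sided alpha 0.10 and power 0.80, the normal approximation gives 48 per arm and the t test gives 49 (power 0.804). The stated 49 per arm reproduces.

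**Step 2: variance due to sex.** With equal numbers of men and women in each arm, sex contributes g²/4 to the residual variance. Holding the total residual SD at 7.07 (variance 50), the share is r² = (g²/4)/50.
- g = 2: 1/50 = 0.02
- g = 4: 4/50 = 0.08

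**Step 3: standard error.** Without sex, the SE is 7.07 × √(2/49) = 1.429. The SE that fits the stratified design is √(1 − r²) times this.

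**Step 4: actual alpha without sex.** 2 × (1 − Φ(1.645/√(1 − r²))).

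**Step 5: power.** 3.6/1.429 = 2.52.
- Without sex: Φ((2.52 − 1.645)/√(1 − r²))
- With sex: Φ(2.52/√(1 − r²) − 1.645)

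| g (mmHg, assumed) | r² | √(1 − r²) | SE overstated by | Actual alpha without sex | Power without sex | Power with sex | Gain (points) |
|---|---|---|---|---|---|---|---|
| 0 | 0 | 1.000 | 0% | 0.100 | 0.809 | 0.809 | 0 |
| 2 | 0.02 | 0.990 | 1.0% | 0.097 | 0.812 | 0.816 | 0.4 |
| 4 | 0.08 | 0.959 | 4.3% | 0.086 | 0.819 | 0.837 | 1.8 |

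The overstatement is 1/√(1 − r²) − 1.

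**Step 6: simulation check.** Sex-stratified permuted blocks (sizes 2, 4 and 6 assumed), 98 patients, baseline slope 0.6 and baseline SD 10 (both assumed), total residual SD 7.07, 8,000 runs per setting. The Monte Carlo error on a 10% rate is √(0.1 × 0.9/8000) = 0.003.
- g = 0: type I error 0.103 without sex and 0.102 with; power 0.800 and 0.801.
- g = 2: type I error 0.097 and 0.101; power 0.804 and 0.810.
- g = 4: type I error 0.090 and 0.105; power 0.813 and 0.831. With no treatment effect, the model without sex reported a mean SE of 1.434, while its estimate varied with an SD of 1.40 (1.37 in the runs with a treatment effect). The model with sex reported 1.375.

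The simulation agrees with the formulas in direction and approximate size.

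**The case against.** The strongest reply is that the consequence is conditional and small. Baseline nocturnal systolic BP is already in the model and will carry much of any stable sex difference. The population is also narrow: grade 1 hypertension, age 50 to 75, women postmenopausal. No adjusted sex difference is documented, and an assumed 4 mmHg already exceeds the 3.6 mmHg treatment effect. The error is conservative, the design still reaches its 0.80 power in every case above, the study is described as exploratory, and the sex- and age-adjusted model will be reported anyway. All of this stands, and it limits the point to a minor one. It does not explain why the stratification factor is missing from the test that counts.

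Three stronger readings are tempting, and the documents do not support them.
- A reader might infer that the primary interval and p value are certainly too wide. That needs a sex effect given baseline, which the protocol does not report. With none, nothing is lost.
- A reader might take a residual SD of 5.0, where the deflation of alpha looks larger: at 2 and 4 mmHg the SE is overstated by about 2% and 9%, and alpha is 0.093 and 0.073. Power at that SD is already about 97% without sex, so the loss is at most about 0.6 points. Alpha from one SD should not be set beside power from the other.
- A reader might infer that the subgroup analysis means two separate tests, one in each sex. The text says only "Subgroup analysis is planned for sex" and gives no method, which an article may leave to the full analysis plan.

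**Conclusion.** The mismatch between the stratified design and the primary model is real and is stated in the text. Its effect is conditional: only if sex predicts week-8 nocturnal systolic BP given baseline is the primary standard error too large and the test mildly conservative. At the SD behind the sample size and 49 per arm, an assumed sex difference of 2 to 4 mmHg costs about 1 to 4% in the standard error and 0.4 to 1.8 points of power.

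These figures assume equal numbers of men and women and near-complete sex balance among the 98 analysed patients. The estimate is unbiased, type I error is not inflated, and the sample size need not rise. This is a nearly free improvement of minor size; it does not invalidate the planned test.

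**What to change.** Before unblinding, change the primary model in the Data analysis section to: week-8 nocturnal systolic BP = group + baseline nocturnal systolic BP + sex. Keep the model without sex as a sensitivity analysis.

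The cost is one sentence and one degree of freedom: with 98 patients the residual degrees of freedom go from 98 − 3 = 95 to 94. Sex is already recorded for the stratification, so no new data are needed, and if sex has no effect given baseline the loss is negligible.

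### Sex is the stratification factor but is left out of the primary ANCOVA, so the primary standard error is somewhat too large if sex predicts week-8 nocturnal systolic BP beyond baseline

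*Protocol article*

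**What the plan says.** The Randomization section describes the allocation lists as using "sex stratification, randomly varying block sizes". Sex is the only stratification factor named, and the inclusion criteria ask for equal numbers of men and postmenopausal women.

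The Data analysis section fixes the confirmatory model: "An analysis of covariance (ANCOVA) adjusted for baseline systolic BP values using group allocation as a factor will be applied". The test level follows: "The global two-sided significance level is 0.1". Sex then appears in two supporting places. One is a model that adds it together with age ("A sensitivity analysis to the primary efficacy ANCOVA model will be applied with additional covariates/factors given by age and sex"). The other is a subgroup analysis ("Subgroup analysis is planned for sex"). The article gives no reason for leaving the stratification factor out of the primary model. Because that model is written out in full, this is not a detail left to an unseen analysis plan.

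**The concern.** Stratified blocks make the two arms almost equal in their mix of men and women. Any difference between the sexes in week-8 pressure therefore nearly cancels in the treatment comparison and adds almost nothing to the true sampling variance of the estimate. A model without sex does not know this. Whatever part of the sex difference baseline does not explain stays in its residual, and the standard error is computed from that residual. The reported standard error then exceeds the true variability of the estimate, the confidence interval is too wide, and the test rejects less often than its nominal 10%.

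What is at stake is precision that the design has already paid for. The trial is planned at 80% power with a 10% two-sided level, and the Discussion calls recruitment challenging, with about 8 of 10 candidates failing pre-screening.

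**Working it through.** **Reproducing the plan's figure.** The Power calculation section starts from "a mean decrease in systolic BP of 3.8 mmHg with a standard deviation of 5.0 mmHg in the probiotic group" and a placebo decrease of 0.2 mmHg with the same SD. The difference is 3.8 − 0.2 = 3.6 mmHg. The SD used is √2 × 5.0 = 7.07 mmHg, so the standardised effect is 3.6/7.07 = 0.51. At two-sided 0.10, a noncentral t calculation gives power 0.797 at 48 per arm and 0.804 at 49 per arm. That matches the stated result ("with a power of 0.8 at a two-sided significance level of 0.1 is given by 98 patients"). For 10% dropout, 98/0.9 = 108.9, so 110 is adequate.

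**Size of the standard error excess.** The inputs are:
- σ, the residual SD with sex in the model: 7.07, so σ² = 50 (Power calculation);
- equal numbers of each sex (inclusion criteria);
- g, the sex difference in week-8 nocturnal systolic BP remaining after baseline adjustment: **assumed**, as the article gives none.

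With a 1:1 sex ratio, the omitted factor adds g²/4 to the residual variance. Stratification keeps the true variance of the estimate at the σ² level. The ratio of reported to correct standard error is therefore √(1 + g²/(4σ²)). The actual level of the nominal 10% test is the two-sided t tail (95 df) at 1.661 × ratio.

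| g (mmHg) | ratio | SE excess | actual level |
|---|---|---|---|
| 0 | 1 | 0% | 10% |
| 3 | √(1 + 9/200) = 1.022 | 2% | 9.3% |
| 5 | √(1 + 25/200) = 1.061 | 6% | 8.1% |
| 8 | √(1 + 64/200) = 1.149 | 15% | 5.9% |

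A simulation of 6,000 sex-stratified trials at g = 5 and σ = 7.07 rejected 8.3% under the null without sex and 10.0% with it.

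**If 7.07 is instead the residual SD without sex.** Then σ² = 50 − g²/4. Simulation used 98 patients, sex-stratified blocks of 4 or 6, and 5,000 runs per setting:

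| g (mmHg) | mean model SE, no sex | true SD of estimate, no sex | null rejection, no sex / with sex | power, no sex / with sex |
|---|---|---|---|---|
| 0 | 1.431 | 1.427 | 0.099 / 0.100 | 0.806 / 0.806 |
| 4 | 1.432 | 1.374 | 0.087 / 0.100 | 0.806 / 0.826 |
| 6 | 1.434 | 1.316 | 0.072 / 0.105 | 0.820 / 0.862 |

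On this reading the planned model keeps at least 80% power, and adding sex raises it. On the first reading, a noncentral t calculation gives the model without sex a power of 0.794 at g = 3, 0.775 at g = 5 and 0.729 at g = 8. The model with sex has 0.804. In both cases 49 per arm reaches the stated power once sex is in the model.

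**What baseline already removes.** Suppose men and women differ by the same D at baseline and at week 8, with an assumed within-sex SD of S = 10 and within-sex correlation ρ. The residual variance without sex is V − C²/V, where V = S² + D²/4 and C = ρS² + D²/4. With sex it is S²(1 − ρ²). For ρ = 0.7 and D = 8:
- V = 100 + 16 = 116 and C = 70 + 16 = 86;
- without sex: 116 − 86²/116 = 52.24;
- with sex: 51;
- ratio √(52.24/51) = 1.012.

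Over D = 2 to 8 and ρ = 0.5 to 0.875 the ratio runs from 1.000 to 1.023. If sex acts only through baseline, the ratio is exactly 1.

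**The case against.** The strongest case against is that the effect is probably small. The baseline covariate is already in the model, and a stable sex difference leaves only a 0–2% excess. A remaining difference of 5 or 8 mmHg would exceed the whole planned treatment effect of 3.6 mmHg. The error is on the safe side, and a sex-adjusted estimate will be reported anyway through the sensitivity model. All of this stands. It limits the size of the point but does not remove the mismatch between design and analysis, for which the article gives no reason.

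Some stronger readings are tempting but unsupported:
- **The standard error is too large whenever sex predicts nocturnal BP.** Only prediction beyond baseline matters, because baseline is in the model.
- **The excess should be computed at an SD of 5.0.** The same formula would then give √(1 + 9/100) = 1.04, √(1 + 25/100) = 1.12 and √(1 + 64/100) = 1.28 for 3, 5 and 8 mmHg. The article does quote 5.0 for each group's decrease, but its sample size rests on 7.07.
- **The plan leaves two competing primary results.** The Data analysis section names one primary model and labels the other a sensitivity analysis.
- **Treated or untreated status should be handled in the same way.** It is not a stratification factor, so this argument does not reach it.

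**Conclusion.** The point holds as a minor but certain mismatch: the one stratification factor is missing from an explicitly stated confirmatory model. Its consequence is conditional. If sex predicts week-8 nocturnal systolic BP given baseline, the primary analysis is conservative and loses some precision. A reader might infer that the primary result would be biased, that its false-positive rate would rise, or that the sample size is wrong. None of these follows: balance by sex protects the estimate, the error lowers the rejection rate, and the stated 98 reproduces.

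The percentages rest on assumed sex effects, an equal sex ratio and the plan's SD of 7.07. The design mismatch does not depend on those assumptions. The most plausible excess is at the low end, because a sex difference that persists from baseline to week 8 is mostly absorbed.

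**What to change.** State the primary model as week-8 nocturnal systolic BP = group + baseline nocturnal systolic BP + sex. Keep age as the added covariate in the sensitivity model. Include sex in the multiple-imputation model too, so that it matches the analysis model. Record the change before unblinding.

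The cost is one model term and one degree of freedom, with no new data and no change to the sample size. If sex has no effect given baseline, almost nothing is lost: the simulated mean standard error at g = 0 was 1.4308 without sex and 1.4311 with it.

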## Discussion

With this study, we want to close the gap between the existing epidemiological, experimental, and our own clinical data in healthy volunteers. We will do this by thoroughly investigating the effects of a probiotic that has not been used in hypertensive patients before. However, we do not only aim at alleviating hypertension, we will also use state-of-the-art omics systems approaches to understand the impact of probiotics on the gut microbiome, immunome, metabolome, and vascular phenotypes in these patients. To the best of our knowledge, this is the first study that comprehensively investigates all of these levels in human hypertension.

We hypothesize that targeting the intestinal microbial community with live bacteria will improve hypertension along with an improved immune cell homeostasis. This mode of action could also be effective in treated hypertensive patients who do not reach the desired treatment targets. An improved immune homeostasis could not only lead to lower BP but also to better target organ protection, since immune cells are known to migrate into target organs thereby promoting organ dysfunction. Further, probiotic strains might stably colonize the gut and might evoke—in contrast to classical pharmacological therapy—a long-lasting antihypertensive benefit after discontinuation of treatment. This will be tested in our follow-up phase. Moreover, probiotics are generally well tolerated and have little side effects. Thus, compliance in hypertensive patients, who are skeptical of classical pharmacotherapy, might be improved.

We include either untreated grade 1 hypertensive patients in whom pharmacological treatment can be postponed for a limited time in favor of lifestyle modifications or treated patients who are not on goal despite adequate pharmacotherapy. Included patients have no clinical signs of target organ damage, serious concomitant diseases, or secondary causes of hypertension. From our point of view, these mildly hypertensive patients would benefit most from a probiotic intervention. Furthermore, according to applicable guidelines, it is possible to delay the start or change of pharmacotherapy for the 12-week study duration at this stage of the disease. This choice will limit the extrapolation of our results to other hypertension grades, such as patients with resistant hypertension. However, these patients have a higher risk for cardiovascular events, and necessary therapeutic changes cannot be postponed.

Interventional considerations were based on a meta-analysis that suggested an intervention period of ≥ 8 weeks with ≥ 10^11^ CFU/day of a multi-strain probiotic to effectively lower BP [9].

We chose nocturnal BP instead of office BP or 24-h ambulatory BP measurement to achieve a highly standardized measurement in the patient’s natural environment. This standardized measurement, which excludes variations due to physical activity during the day, allows to conduct this study with a medium sample size.

Although there is a high level of interest among eligible patients, recruitment turned out to be rather challenging. This is mainly due to the fact that BP is highly variable within subjects. About 8 of 10 candidates fail our pre-screening, because they cannot be classified as grade 1 hypertensive. Recruitment is additionally impeded by common comorbidities, such as insulin-dependent type 2 diabetes or severe obesity. Nevertheless, due to our medium sample size, it is important that demographic, cardiovascular, and metabolic characteristics are well-defined and as narrow as possible.

All biomaterials, in particular, stool samples, are collected with the highest scientific standards to allow for high-quality microbiome analyses [23].

In conclusion, probiotic treatment of patients with grade 1 hypertension has the potential to lower BP. Due to its innovative mode of action, probiotic treatments could be considered for prevention, might delay pharmacotherapy, and enable dose reduction of antihypertensive drugs, and thereby contribute to target organ protection and the reduction of cardiovascular events.

